#### Provisions for post-trial care {30}

No direct compensation will be allocated to participants.

### Outcomes {12}

The primary objective of this study is to demonstrate feasibility, inclusive of enrollment, randomization, intervention allocation, and monitoring of a randomized controlled trial. This will include the following outcome measures:
*Capability of enrollment* will be determined by an average of ≥1 patients enrolled per week.
We will also assess following outcomes: proportion of patients risk stratified and screened, proportion of eligible individuals consenting to involvement in this study, and proportion of recruited individuals who are enrolled in the study.*Feasibility of the randomization processes* will be evaluated determined by ≥90% of enrolled high-risk patients randomized to an intervention or control group.*Feasibility of blinding* of participant, care provider, investigator, and outcomes assessor to the intervention allocation of participants will be evaluated by ≥80% of respondents not aware of allocation as indicated in a survey to assess their knowledge of which patients received the intervention and placebo.*Intervention delivery* will be assessed by determining if protocol adherence rates exceed ≥90% and recording observational data on the quality of intervention delivery using a data collection sheet.*Monitoring of protocol deviation and compliance* measured by the frequency, rate, and rationale of events when study activities diverge from the REB-approved protocol.*Monitoring of safety* will be assessed by determining the rate and efficiency of reporting adverse events if they occur and monitoring adherence rates to safety and monitoring protocols.*Feasibility of data extraction analysis* will be determined if the required data could be abstracted for ≥90% of patients: medication use, incidence of postoperative atrial fibrillation, postoperative outcomes, etc.*Resources* required to conduct a future multicenter PREP-AF trial will be assessed by evaluating the administrative capacity of the POAF research team, including the required number of hours of research assistant time, as well as the feasibility of the designated study budget.

Secondary clinical outcomes will include the incidence and severity of POAF (defined as an irregularly irregular atrial rhythm without clear P waves, recorded on a standard 12-lead electrocardiogram (ECG) that occurred in the immediate 30-day postoperative period [3]), and classified in severity by the Ottawa Thoracic Morbidity and Mortality (TM&M) system [3]; hospital length of stay; and incidence of other postoperative complications using the taxonomy of the TM&M definitions [3].

### Participant timeline {13}

Below is a schedule of activities that would be involved in trial participation:

**Table Tabb:** 

	Study period							
	Enrolment	Allocation	Post-allocation					Close-out
	Screening visit	Screening visit	Preoperative anesthesia visit		Operative hospital admission		30-day follow-up	
Timepoint**	***-t***_***1***_	0	***t***_***1***_	***t***_***2***_	***t***_***3***_	***t***_***4***_	***etc.***	***t***_***x***_
**Enrolment:**								
**Eligibility screen**	X							
**Informed consent**	X							
**Allocation**		X						
**Interventions:**								
***Amiodarone***					X			
***Control***					X			
***Standard of care***					X			
**Assessments:**								
Medical history, medication, demographics	X	X						
Height and weight, ECG			X	X				
Postoperative outcomes; adverse event review and evaluation					X	X	X	X
Complete case report forms	X	X	X	X	X	X	X	X

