### Eligibility criteria {10}

All patients undergoing thoracic surgery will be screened for eligibility. In order to participate, patients must provide consent if “high-risk” of POAF, be ≥18 years, and undergoing major non-cardiac pulmonary or esophageal surgery at the Ottawa Hospital during the 1-year time period.

Patients will be excluded if they are <18 years; are pregnant; have a history of atrial arrhythmia, Wolf-Parkinson-White syndrome (WPW), or 2nd or 3rd degree heart bock without a pacemaker; are currently on antiarrhythmic therapy; have a previous severe adverse reactions or contraindications to amiodarone; have QTc interval longer than 450ms; or have serum alanine transaminase or aspartate transaminase over 3 times the upper limit of normal, or Child-Pugh class C liver dysfunction.

Patients enrolled in other clinical trials are potential candidates for PREP-AF feasibility.

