#### Recruitment {15}

Eligibility criteria will first be assessed by the thoracic surgery physician team (surgeon, fellow, and/or resident) and the research coordinator at the time of the preoperative thoracic surgery clinic visit. All eligible individuals will be approached for participation in the trial initially by their thoracic surgery physician team after consenting to major thoracic surgery, and if interested, then approached by a research coordinator immediately after their thoracic surgery clinic visit. During this screening visit, the research coordinator will discuss the study protocol, review eligibility criteria, and assess willingness to participate. If the individual is “high-risk”, a consent discussion will be initiated, including a discussion of the risk and benefits of participating in the trial as outlined in the consent form. Their questions will be answered, and if interested and willing, then written informed consent will be obtained and the research coordinator will enroll the patient in the study.

If “low-risk”, no formal consent discussion will be conducted and the patient will continue with standard of care.

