### Assignment of interventions: allocation

#### Sequence generation {16a}

After written informed consent is obtained, high-risk patients will be randomly assigned to either the intervention or control group by the clinical trial Pharmacy Research Technician using a secure web-based randomization system at the Methods Centre of The Ottawa Hospital Research Institute. Randomization will be stratified according to pre-randomization beta-blocker use. Allocation bias will be prevented by using a randomization table with variable blocks of 4 and 6.

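### The schedule allocates patients at the screening visit but places the only ECG after allocation, so the QTc exclusion could be checked only once a patient is already randomised

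*Protocol article*

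**What the plan says.** Protocol article, Participant timeline {13}: the first two columns, at -t1 and 0, are both headed as the screening visit. "Eligibility screen" and informed consent are marked at -t1, and allocation at 0. The next two columns, t1 and t2, come under the post-allocation heading, with the visit label "Preoperative anesthesia visit". The row "Height and weight, ECG" is marked at t1 and t2 and nowhere else. Amiodarone and control are marked at t3, the operative admission.

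Eligibility criteria {10}: patients are excluded if they "have QTc interval longer than 450ms".

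Recruitment {15}: "Eligibility criteria will first be assessed by the thoracic surgery physician team" and the research coordinator, at the preoperative clinic visit. Interested patients are "then approached by a research coordinator immediately after their thoracic surgery clinic visit", and the coordinator reviews eligibility, takes written consent and enrols.

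Sequence generation {16a}: "After written informed consent is obtained, high-risk patients will be randomly assigned to either the intervention or control group". No ECG step or condition is stated.

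**The concern.** An exclusion criterion has to be settled before randomisation. Here the one criterion that cannot be judged without an ECG comes, in the schedule, before the only ECG. The text does not repair the order: it goes from eligibility review to consent to randomisation without saying that an ECG must be in hand. Nor does the article say how a randomised patient is handled if the later ECG breaches the criterion.

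Three things are at stake.

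- **Feasibility measures.** Outcomes {12} sets a target of at least 90% of enrolled high-risk patients randomised and at least 90% protocol adherence, and also tracks protocol deviations. Randomising before eligibility is complete makes the first target easier to reach. It may push failures into the other two, so the measures no longer separate screening problems from delivery problems.
- **Vanguard data.** Statistical methods {20a} plans to carry the results into a full-scale trial analysed by intention to treat. Patients who should not have been randomised would go with them.
- **A safety-related exclusion.** The protocol lists QT prolongation among the risks of amiodarone, so this is not an incidental criterion.

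**Working it through.** There is no figure of the plan's own to reproduce: Sample size {14} states that no calculation was done. The check is on the order of events, followed by an illustration of scale.

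**Step 1. Order of events in the schedule (columns counted from the left).**

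| Event | Column | Visit |
|---|---|---|
| Eligibility screen, consent | 1 (-t1) | Screening |
| Allocation | 2 (0) | Screening |
| ECG | 3 and 4 (t1, t2) | Preoperative anesthesia, post-allocation |
| Amiodarone or control | 5 (t3) | Operative admission |

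A table broken in extraction does not explain this. The marks line up with the headings, and study drug falls at the operative admission, which agrees with the infusion starting at induction in Intervention description {11a}.

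**Step 2. Does the text change the order?** Recruitment {15} puts eligibility review and consent at the clinic and screening contact. Sequence generation {16a} and Implementation {16c} put randomisation after consent and enrolment. None of the three mentions an ECG. The text therefore fits the table and adds no safeguard.

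**Step 3. Which criteria need the ECG?** QTc longer than 450 ms does. The rhythm and conduction items are worded as "have a history of atrial arrhythmia, Wolf-Parkinson-White syndrome (WPW), or 2nd or 3rd degree heart bock without a pacemaker". They can be read as history items, and medical history is collected at -t1. The argument therefore rests on QTc alone.

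**Step 4. Scale.** Inputs: n = 80 to be randomised (Sample size {14}), and p = the share of otherwise eligible patients with QTc above 450 ms. The documents do not give p. The values below are assumptions, and they apply only if no ECG is read before allocation.

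Expected number = 80 × p. Chance of at least one = 1 − (1 − p)^80.

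| Assumed p | Expected among 80 | Chance of at least one |
|---|---|---|
| 1% | 0.8 | 1 − 0.99^80 = 55% |
| 2% | 1.6 | 1 − 0.98^80 = 80% |
| 5% | 4 | 1 − 0.95^80 = 98% |
| 10% | 8 | 1 − 0.90^80 = more than 99.9% |

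Even at 1%, at least one such patient is somewhat more likely than not. The table shows only that the question is not remote. It does not estimate how many there will be.

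**The case against.** The strongest reply is that eligibility is marked before allocation and is reviewed by both the surgical team and the coordinator before consent. Nothing forbids them from using an ECG already on file. The schedule is also coarse, with placeholder timepoints and two ECG marks under one visit label, and the text names no visit for randomisation, so this may be an imprecise table and not a faulty design. This stands in part. A reader might infer that ineligible patients will be randomised, but the documents support only that they could be. The reply does not remove the conflict, because the article states a sequence that does not fit its own exclusion and nowhere requires an earlier ECG.

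Several stronger readings are tempting and should not be drawn.

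- **Other criteria.** Heart block, WPW and atrial arrhythmia come under a history wording. Current atrial arrhythmia is not listed as a separate exclusion. The heart rate in the risk score is not tied to an ECG. Liver enzymes have no row at any timepoint, which is detail an article commonly leaves to the full protocol and not a wrong order.
- **Dosing against the exclusion.** Study drug starts after the scheduled ECG, so the result could be known first. The article leaves the handling of such a patient unstated, but it does not provide for dosing one.
- **A breach of intention to treat.** That principle is stated for the anticipated full-scale trial and keeps patients who never received treatment. No section says that such patients are dropped.
- **Failure of the adherence target.** Outcomes {12} gives no denominator for adherence, which could be patients or doses. The share of the 10% margin that late exclusions would use cannot be calculated.

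**Conclusion.** The concern holds in a limited form. As scheduled, allocation precedes the only ECG, although QTc longer than 450 ms is an exclusion and the text puts no ECG condition before randomisation. QTc-ineligible patients could therefore be randomised and found ineligible only afterwards, which would affect the feasibility and adherence measures and the vanguard data. The size is unknown. The expected 0.8 to 8 of 80 rests on an assumed prevalence of 1% to 10% and on no ECG being read before allocation. If a recent ECG is in practice reviewed at screening, the defect is one of documentation. If it is not, it is a defect in the order of trial procedures. In both cases the sections conflict and should be reconciled before patients are randomised.

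**What to change.** Reconcile Eligibility criteria {10}, Participant timeline {13}, Recruitment {15} and Sequence generation {16a} so that randomisation takes place only once the QTc criterion is confirmed. There are two routes:

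1. Take consent at the clinic as now, and allocate after the ECG already scheduled at the preoperative anesthesia visit. This needs no extra procedure.
2. Keep allocation at the screening visit, but require a qualifying ECG before it and mark that ECG in the schedule.

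Under either route, make confirmed eligibility a condition for the pharmacy technician to randomise. State also that any patient still found ineligible after allocation stays in the as-randomised set and is reported with the reason.

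The first route needs one consequential edit. Patients are now enrolled at consent, so those who fail the QTc check before allocation would count against the target of at least 90% of enrolled patients randomised. Define enrolment for that target as consent with eligibility confirmed, and report the QTc screen failures separately.

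The cost is a change to the table and a few sentences. The first route also leaves the pharmacy less time to prepare study drug. The second may require an ECG earlier than now planned for patients who have none on file.

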#### Sample size {14}

No sample size calculation was conducted for this feasibility study. We aim to recruit 80 patients for randomization during this 12-month trial. Our institution conducts approximately 200 major thoracic surgeries annually and we anticipate 100 of those patients to be eligible for inclusion based on POAF risk and assume a recruitment rate of 80. Patients will follow the schedule activities described in the “Participant timeline {13}” section including a 30-day follow-up.

#### Recruitment {15}

Eligibility criteria will first be assessed by the thoracic surgery physician team (surgeon, fellow, and/or resident) and the research coordinator at the time of the preoperative thoracic surgery clinic visit. All eligible individuals will be approached for participation in the trial initially by their thoracic surgery physician team after consenting to major thoracic surgery, and if interested, then approached by a research coordinator immediately after their thoracic surgery clinic visit. During this screening visit, the research coordinator will discuss the study protocol, review eligibility criteria, and assess willingness to participate. If the individual is “high-risk”, a consent discussion will be initiated, including a discussion of the risk and benefits of participating in the trial as outlined in the consent form. Their questions will be answered, and if interested and willing, then written informed consent will be obtained and the research coordinator will enroll the patient in the study.

If “low-risk”, no formal consent discussion will be conducted and the patient will continue with standard of care.

### Assignment of interventions: allocation

#### Sequence generation {16a}

After written informed consent is obtained, high-risk patients will be randomly assigned to either the intervention or control group by the clinical trial Pharmacy Research Technician using a secure web-based randomization system at the Methods Centre of The Ottawa Hospital Research Institute. Randomization will be stratified according to pre-randomization beta-blocker use. Allocation bias will be prevented by using a randomization table with variable blocks of 4 and 6.

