### Trial design {8}

The PREP-AF feasibility trial is a pragmatic single-center, parallel group, double-blinded, randomized controlled feasibility study.

Individuals will first be assessed for their risk of POAF based on their POAF prediction score (Table 1) and planned procedure.

**Table 1 Tab1:** POAF prediction score [15, 17]

Criteria	Points
Male gender	1
HR^a^ >72 bpm	1
Age 55–74 years	3
Age >75 years	4
Total	/6

^a^Heart rate (HR)

Individuals will be considered “high-risk” of POAF by meeting both of the following criteria: (1) POAF prediction score greater than or equal to 4 (Table 1) and (2) undergoing lobectomy, extended lobectomy, pneumonectomy, or esophagectomy.

High-risk individuals will be randomized 1:1 to intervention or control group.

Individuals will be considered “low-risk” of POAF by one the following criteria: (1) POAF prediction score less than 4 (Table 1) or (2) undergoing gastrectomy or sublobar resection.

Low-risk individuals will receive standard care with monitoring for clinical outcomes and adverse events.

Patients using beta-blockers at the time of enrollment will be eligible to participate in the trial. Given that beta-blocker use is protective against development of POAF, we will stratify these patients at the time of randomization to ensure the proportion of beta blocker usage is equal between intervention groups.

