### Statistical methods

#### Statistical methods for primary and secondary outcomes {20a}

The primary end point of this study is feasibility so no in-depth statistical analysis is planned. However, for the anticipated full-scale trial to follow, we plan to conduct analysis using an intention-to-treat, considering all patients as randomized regardless of whether they received the randomized treatment. Patients will be administered the intervention while admitted to hospital following major thoracic surgery so we anticipate very few patients to crossover or be lost to follow-up. To reduce the risk of missing data, we will capture data from patient’s health records, surveys, and manual chart review. Any departures from the protocol will be documented in the participant file, reviewed, and compared quantitatively. Reasons for missing data will be recorded, and if missing data is >5%, multiple imputation methods will be used to address missing data in the analysis.

The statistical analysis will be performed using statistical software program R version 3.5.3. Continuous data that are normally distributed will be analyzed with an unpaired Student’s t-test. Non-continuous data will be analyzed with a chi-squared or Fisher’s exact test as appropriate. Level of significance will be determined by *p* < 0.05.

We plan to use this as a vanguard study. If a full-scale trial is completed, we plan to incorporate the results of this study into the data collection of a full-scale trial.

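### Randomisation is stratified by beta-blocker use, but the tests named for the clinical outcomes ignore the stratum: a small mismatch that one sentence would remove

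*Protocol article*

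**What the plan says.** Trial design {8} gives the reason for stratifying: "Given that beta-blocker use is protective against development of POAF, we will stratify these patients at the time of randomization". The aim stated there is balance: "to ensure the proportion of beta blocker usage is equal between intervention groups". Sequence generation {16a} confirms the factor ("Randomization will be stratified according to pre-randomization beta-blocker use") and uses permuted blocks of 4 and 6 patients.

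Statistical methods {20a} names the tests. For binary outcomes: "Non-continuous data will be analyzed with a chi-squared or Fisher’s exact test as appropriate". For continuous outcomes: "Continuous data that are normally distributed will be analyzed with an unpaired Student’s t-test". Significance is set at p < 0.05, with no statement of sidedness. The only additional analysis named in the article is a subgroup analysis by procedure type {20b}. No section of the article mentions a stratified test or adjustment for beta-blocker use.

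Three other statements set the context. The primary endpoint is feasibility, and no in-depth statistical analysis is planned {20a}. POAF incidence is a secondary outcome {12}. The results are to be taken into the data of a full-scale trial if one is completed {20a}.

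**The concern.** When randomisation is stratified on a factor that predicts the outcome, the arms are balanced on that factor by design, and the true sampling error of the treatment difference no longer contains the variation between strata. A test that ignores the strata still counts that variation in its standard error. In large samples it is slightly conservative and gives up a little power.

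The protocol itself calls the factor protective against POAF, so the condition for this effect is met on its own terms. The article did not leave the method open: it names tests, and those tests do not match the design. At stake are the coherence of the POAF comparison with the randomisation and, if the data are retained for a larger trial, a small amount of power there.

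**Working it through.** **Inputs from the article.** 80 patients randomised 1:1, so 40 per arm {14}. POAF rate 12.3% in the high-risk group and assumed risk ratio 0.22 (Prediction of POAF). Significance level 0.05, taken as two-sided.

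**Inputs not in the article, assumed.** Beta-blocker prevalence 20% to 40%, and an odds ratio of beta-blocker use for POAF between 0.25 and 0.7. For a larger trial: either 117 per arm, which gives 80% power for 12.3% against 2.7%, or 350 per arm with 15% POAF in non-users and a risk ratio of 0.5.

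**Step 1. The article's own figures reproduce.** 0.123 × 0.22 = 0.027, and 1/(0.123 − 0.02706) = 10.4. These are the stated 2.7% and NNT of 10.4. There is no stated power to reproduce.

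**Step 2. Events in the pilot.** 40 × 0.123 = 4.9 in the control arm and 40 × 0.027 = 1.1 in the amiodarone arm, about 6 in all.

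**Step 3. Share of the outcome variance due to the stratum.** With stratum weights w and stratum rates p_s, the share is 1 − Σ w·p_s(1 − p_s) / [p(1 − p)].

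- At an overall rate p = 0.123, the share is 0.2%, 0.6% and 1.3% for 20% users (odds ratio 0.7, 0.5, 0.3), and 0.3%, 1.1% and 2.7% for 40% users.
- Worked case, 40% users and odds ratio 0.3: the rates are 0.167 in non-users and 0.057 in users. Then 0.6 × 0.167 × 0.833 + 0.4 × 0.057 × 0.943 = 0.105, against 0.123 × 0.877 = 0.108. The unrounded ratio gives 2.7%.
- At 15% in non-users, 40% users and odds ratio 0.25, the share is 2.9%.

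**Step 4. Size of the unstratified test in large samples.** The statistic's true standard deviation is √(1 − share). With a share of 2.9%, 1.96/√0.971 = 1.989, which gives a two-sided size of about 4.7%.

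**Step 5. Power by simulation, unstratified chi-squared against Cochran-Mantel-Haenszel (CMH).** At 350 per arm, with 200,000 runs per setting:

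| Users | Odds ratio | Unstratified | CMH |
|---|---|---|---|
| 40% | 0.25 | 75.2% | 76.0% |
| 40% | 0.5 | 80.9% | 81.1% |
| 20% | 0.25 | 83.1% | 83.4% |
| 20% | 0.5 | 85.4% | 85.5% |

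A separate run of 40,000 for the first row gave 75.0% and 75.7%, so the largest gain is about 0.7 points. Size under the null in that row was 4.7% against 4.9%.

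At 117 per arm, CMH ranged from about 0.8 points lower to 0.2 points higher.

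At 40 per arm, CMH had 1 to 3 points less power. In runs of 3,000, it was 0.37 to 0.39 against 0.39 to 0.40 for chi-squared. Part of that difference reflects size: at 40 per arm the null size was about 5.5% for chi-squared and 5.0% for CMH. Fisher's exact test, which the article also allows, had power of 0.19 to 0.21 there.

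**The case against.** The strongest reply is that nothing of substance is lost. Most of it stands.

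- The stated purpose of stratifying is balance, and balance is kept whichever test is used. A reader might infer that the sponsor stratified to gain precision and then threw it away. The article makes no such claim.
- A reader might also infer that these tests are fixed for the full-scale trial. The article does not say so. For that trial it commits expressly to intention-to-treat analysis and to incorporating these results. The paragraph naming the tests does not mention the full-scale trial.
- In the trial actually planned, the stratified test has no power advantage, the tests serve secondary outcomes only, and the larger-trial figures rest on assumptions.
- Beta-blocker use is called protective for POAF only, so the argument does not extend to the t-test for outcomes such as length of stay.
- The beta-blocker stratum will be sparse. With 20% to 40% users and odds ratios of 0.3 to 0.7, it would hold roughly 0.5 to 2 expected events. For example, with 40% users and a control rate of 0.101, 16 × 0.101 × 1.22 = 2.0. An asymptotic stratified test is then unreliable, so any fix must allow an exact one.

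It can also be said that adjustment for strata is commonly left to an analysis plan that is not shown. That would answer silence. It answers less well a section that names specific tests, all of them unstratified.

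**Conclusion.** The mismatch is real and minor. The design stratifies on a factor the protocol calls protective against POAF, and every test named in {20a} ignores it. The tests remain essentially valid, and their large-sample error is on the conservative side. The loss is at most about 0.7 points of power, with a true size of about 4.7%, in the least favourable setting examined (350 per arm, 15% POAF in non-users, 40% users, odds ratio 0.25, risk ratio 0.5). All of those inputs are assumptions. In the 80-patient pilot the benefit of a stratified analysis is coherence with the randomisation, not power. The feasibility conclusions are unaffected. The point is worth acting on because the change is nearly free and because the data may be carried forward, in which case it is better to settle the method before the pilot results are seen.

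**What to change.** In Statistical methods {20a}, add that the secondary comparison of POAF incidence will be stratified by beta-blocker use at randomisation. Report a Mantel-Haenszel risk difference or risk ratio with a 95% confidence interval, and use an exact stratified test when events are sparse. Add that beta-blocker stratum will be kept in the analysis if these data are carried into a full-scale trial. The other outcomes need no change on this ground.

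The cost is one or two sentences. The stratum is recorded for every randomised patient, so no further data or patients are needed.
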